### 2.8. Handling Class Imbalance

To address anticipated class imbalance (recurrence rates within the 0.05–0.25 range), class-weight adjustments will be applied in LR, XGBoost, and MLP models. Decision thresholds will be optimised within validation folds using Youden’s J and F1 score. Predicted probabilities will be calibrated using Platt scaling or isotonic regression, with the choice depending on sample size and distributional characteristics (Platt for smaller samples, isotonic when sufficient data allows). Thresholds used in decision curve analysis will be derived from these probabilities calibrated on validation data to ensure clinically meaningful comparisons.

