The sample sizes derived from steps 1, 2, 3, and 4 were 288, 344, 680, and 459 patients, respectively. We therefore deemed a minimum total sample size of 680 patients necessary for CPR development. Given that our sample size is 2763 patients and the fact that we will perform validation and updating (and not development from scratch), we contend that our regression analyses are adequately powered. Of note, 75% of our dataset (*n* = 2072 patients) will be used for regression model training and the remaining 25% (*n* = 691 patients) will be reserved for testing. The fact our test set alone exceeds the required 680 patients further supports our sample size.

ML and DL techniques are inherently more data-intensive than regression [85]. This is because the number of predictors they consider far exceeds that of regression, even when the same set of predictors is considered, because they examine multiple interaction terms [84]. Unfortunately, guidance for a priori sample size calculations is currently lacking for most ML/DL techniques [86]. However, if closely related data are readily available, it has been suggested that inspecting model learning curves in the related dataset can be valuable to estimate the required sample size for the main dataset [87,88]. We will therefore explore the observed power of our non-regression models by means of learning curves on our non-AF dataset, as well as via a key information theoretic metric: Kullback–Leibler (KL) divergence.

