##### Regularisation Techniques

LR will be instantiated with L2 regularisation (ridge regression). L2 introduces a penalty proportional to the sum of the squared coefficients to the loss function. This shrinks the coefficients of less important features and discourages an overly complex model, thereby stabilising the estimates and improving generalisability.

For XGBoost, we will use built-in tree-specific regularisation hyperparameters to constrain model complexity and mitigate overfitting. See “Hyperparameter Tuning” below.

MLP will be instantiated with L2 (weight decay) and dropout, complementary regularisation techniques that limit the magnitude of weights and prevent complex coadaptation of neurons, respectively. As a result, the network will be prevented from becoming too complex or overly dependent on specific neurons and encouraged to learn more generalised patterns.

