##### Model Building LR and XGBoost

We will instantiate LR with L2 regularisation and default hyperparameters (i.e., C = 1, max_iter = 100, solver = ‘lbfgs’), and XGBoost with default hyperparameters (i.e., n_estimators = 100, learning_rate = 0.1, max_depth = 3, objective = ‘binary:logistic’).

The AF dataset will be randomly split into two parts: training (***T***, 75%) and test sets (***t***, 25%), ensuring that the distribution of outcomes is preserved across both sets. LR and XGBoost models will each be trained, hyperparameter-tuned, and retrained on the training set (***T***), while the independent test set (***t***) will be withheld for final evaluation (Figure 1).

To achieve robust final models, we will employ nested cross-validation (CV) for training and hyperparameter tuning. Nested CV is particularly effective for small to moderately sized datasets because it promotes generalisability by ensuring that the hyperparameter tuning process does not contaminate the internal evaluation phase [113]. To this end, a 5 × 2 setup will be utilised, consisting of 5-fold CV in the outer loop and 2-fold CV in the inner loop (Figure 2). The set ***T*** will first be split into five equal parts. In each fold of the outer loop, one part (20% of ***T***) will serve as the intra-model test set ***T_t_*** while the remaining 80% will serve as the intra-model training set ***T_T_***. Each outer loop iteration will be subjected to an inner loop that further splits ***T_T_*** into two equal parts, using one as the true training set ***T_T_train_*** and the other as the validation set ***T_T_val_***, and alternating them over the two folds. The primary selection metric in the inner CV will be log loss (binary cross-entropy), with ties broken by calibration performance (Brier score).

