Instantiating the models using the hyperparameters determined by the above procedure, we will retrain them in order to leverage all patients in ***T*.** The resulting models will be considered final and subjected to evaluation on ***t*** in the next section (see “Model Evaluation”). At this stage, training performance will be recorded. Specifically, we will report the area under the receiver operating characteristic curve (AUC), F1 score, accuracy, precision, sensitivity, and specificity. Coefficients and ORs (exponentiated coefficients) with 95% confidence intervals (CIs) will be reported for LR, and the hierarchy of predictor variables in descending order of gain (its internal feature importance metric) will be provided for XGBoost. Individual decision trees within the XGBoost model will supplementarily be made available.

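### Class weights combined with tuning on unspecified log loss can push XGBoost to deeper trees and cost it discrimination at low recurrence rates

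*Protocol article*

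**What the plan says.** Section 2.8 expects "recurrence rates within the 0.05–0.25 range" and responds that "class-weight adjustments will be applied in LR, XGBoost, and MLP models". It optimises decision thresholds within validation folds by Youden's J and F1. It adds that "Predicted probabilities will be calibrated using Platt scaling or isotonic regression", without placing that step before or after tuning.

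Model Building LR and XGBoost (section 2.12.6) sets up nested cross-validation "consisting of 5-fold CV in the outer loop and 2-fold CV in the inner loop", and then: "The primary selection metric in the inner CV will be log loss (binary cross-entropy), with ties broken by calibration performance (Brier score". Nothing there says that the loss is class-weighted or scored on recalibrated predictions. Table 2 lets XGBoost choose depth 3, 5, 7 or 9, learning rate 0.01, 0.1 or 0.2, and 50, 100 or 200 trees.

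On size, section 2.7 says "75% of our dataset (*n* = 2072 patients) will be used for regression model training". On LR, "LR will be instantiated with L2 regularisation (ridge regression", and "Coefficients and ORs (exponentiated coefficients) with 95% confidence intervals (CIs) will be reported for LR". No interval method is named.

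**The concern.** Log loss and Brier score reward probabilities that sit at the true event rate. Balanced class weights deliberately move them towards 50%. If the two are combined without a link between them, most of the tuning loss reflects the wrong overall level. A setting can then win by drifting back towards the true level rather than by separating patients better. For boosted trees the way back is depth: deep trees isolate small cells of non-events and push their predicted risk down.

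XGBoost is one of the two primary-analysis models (section 2.12.5), reported on the hold-out set and compared with LR. The plan grades AUC in bands 0.1 wide, so a loss of a few hundredths matters. Recalibration afterwards corrects the risk level. It is monotone, so it cannot repair a ranking lost through the choice of hyperparameters.

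**Working it through.** The plan gives no figure for the effect of weighting, so there is none to reproduce. Its training size follows from 0.75 × 2763 = 2072, which is 104 events at 5% recurrence and 518 at 25%.

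**Inputs.** From the plan: n = 2072, eight predictors, the 36-point XGBoost grid (4 × 3 × 3), 5 × 2 nested cross-validation, and recurrence of 5%, 10% and 25%. Assumed: balanced weights (event-to-non-event weight ratio (1−φ)/φ, that is 19, 9 and 3), the predictor prevalences, and three data models. At 5% recurrence the best achievable AUC under these models is 0.597 (weak), 0.651 (middle, with interactions) and 0.700 (strong).

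**Why raw log loss rewards depth.** For a constant predicted risk p at event rate φ, log loss is −φ ln p − (1−φ) ln(1−p). In the weak model at 5%, tuning by class-weighted loss always chose depth 3, with mean prediction 0.487. Tuning by raw loss gave mean prediction 0.387.
- p = 0.487: 0.05 × 0.7195 + 0.95 × 0.6675 = 0.670
- p = 0.387: 0.05 × 0.9493 + 0.95 × 0.4894 = 0.512

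The change of level alone is worth 0.158. The whole predictive signal in that data model is worth 0.1985 (null) − 0.1956 (true model) = 0.0029, so level swamps signal. In the simulation, raw-loss tuning reached raw log loss 0.6007 against 0.6732, yet after Platt scaling it was worse, 0.1984 against 0.1976.

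**XGBoost test AUC**, 17 to 23 simulated data sets per row:

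| Recurrence | Data model | Weighted, raw loss | Unweighted | Loss |
|---|---|---|---|---|
| 5% | weak | 0.524 | 0.553 | 0.029 |
| 5% | middle | 0.560 | 0.604 | 0.044 |
| 5% | strong | 0.600 | 0.657 | 0.057 |
| 10% | weak | 0.536 | 0.566 | 0.030 |
| 10% | middle | 0.579 | 0.621 | 0.042 |
| 10% | strong | 0.635 | 0.677 | 0.042 |
| 25% | weak | 0.570 | 0.577 | 0.007 |
| 25% | strong | 0.676 | 0.676 | 0.001 |

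Depth 7 or more was chosen in 82–91% of weighted runs against 14–18% of unweighted runs at 5%. At 10% it was 83–100% against 0%. At 25% it was 0–24% of weighted runs. Learning rate 0.2 was never chosen under the weighted, raw-loss rule, so the overfitting comes through depth. Three further sets of runs under similar assumptions gave losses of 0.036, 0.039 and 0.047 at 5% and 0.026, 0.030 and 0.032 at 10%.

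**Recalibration.** Even with Platt scaling fitted on the true population, log loss at 5% was 0.1957–0.1984 for the weighted, raw-loss pipeline and 0.1908–0.1976 unweighted. The null value is 0.1985.

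**LR.** Discrimination did not change (AUC 0.596 against 0.595), and the weighted slopes were essentially unbiased (mean bias within 0.005). For intervals, take balanced weights averaging one and weak effects, so that fitted risks are near 0.5. Per patient, the information is 1/4 and the score variance is (1/4) × 1/[4φ(1−φ)]. Hence model-based SE ÷ true SE = √[4φ(1−φ)]:
- 5%: √0.19 = 0.44
- 10%: √0.36 = 0.60
- 25%: √0.75 = 0.87

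Simulated coverage of a nominal 95% model-based interval was 0.61, 0.76 and 0.92. A sandwich variance restored it to 0.95, 0.945 and 0.96.

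**The case against.** **The order of steps is open.** Section 2.8 speaks of probabilities calibrated on validation data, and the only set named as a validation set is in the inner loop. Recalibration might therefore precede scoring, and the weighting scheme is not given either. This stands as a limit: the harm is conditional on raw, unweighted scoring. But the selection rule is written out in full and says nothing of recalibration or weighting, so raw log loss is its natural reading, and the two options give materially different models.

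**The harm depends on the event rate.** This stands. At 25%, inside the plan's own range, the loss is negligible.

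**A reader might infer that the clinical point scores are degraded too.** This is not supported. CPR Development turns mean SHAP values into one to three points through percentile tiers, which discards most of the model's fine ranking. When those tiers were applied to both pipelines, the point score's AUC (weighted against unweighted) was 0.591 against 0.583 at 5%, 0.602 against 0.592 at 10% and 0.602 against 0.603 at 25%. A separate run gave 0.601 against 0.597 at 5% and 0.591 against 0.584 at 10%. The tier check covered main effects only, without the zero-point or interaction rules. It shows no harm there and does not settle the augmented scores.

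**A reader might infer that the planned odds-ratio intervals are wrong.** The plan names no interval method, so this holds only if model-based standard errors are used. Sandwich intervals are sound; a bootstrap was not tested.

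**Conclusion.** The point holds in a limited form. As written, the class weights and the tuning rule work against each other. With balanced weights and raw log loss, the XGBoost model loses about 0.03 to 0.06 of AUC at 5–10% recurrence and less than 0.01 at 25%. Later calibration does not recover it. What suffers is the XGBoost model reported under Model Evaluation Test Set and its comparison with LR, which weighting leaves untouched on discrimination.

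The figures rest on assumed effect sizes, predictor prevalences and weighting scheme, with few simulated data sets per setting. The direction was the same in every set of runs at 5% and 10%. The MLP was not simulated. The interval issue for LR is a precaution that depends on the method chosen. This is a cheap improvement to a primary-analysis model and does not invalidate the plan.

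**What to change.** Preferred: remove the class weights from section 2.8 and handle imbalance through the thresholds already optimised by Youden's J and F1. In the simulations this raised XGBoost AUC by 0.029 to 0.057 at 5–10% recurrence.

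If weights are kept, add a clause to Model Building LR and XGBoost stating that inner-fold log loss and Brier score are computed on recalibrated predictions, or with the same class weights as training. Scoring after Platt scaling recovered 0.019 to 0.057, and class-weighted log loss recovered 0.030 to 0.051. At 25% no option gained more than 0.008.

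If weights are kept in LR, state that the 95% CIs for the odds ratios come from a sandwich variance or from the unweighted fit.

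The cost is one or two sentences. Without weights, sensitivity and F1 at a 0.5 cut-off will look lower, but the plan optimises its thresholds by Youden's J and F1.

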### 2.9. Ethical Comment and Data Availability

Ethical review and approval were waived for this study due to the anonymised nature of the dataset. Restrictions apply to the availability of the data, which we will access under licence for the sole purpose of this research. This protocol underwent review and received approval from the VISTA-Acute Steering Committee. To access the data, interested parties must likewise submit a proposal to the VISTA-Acute Steering Committee. The dataset was previously inaccessible to all authors.

### 2.10. Code Sharing

The code developed for the study will be made available by the corresponding author upon request, though any code segments that could reveal sensitive aspects of the dataset, such as data cleaning code, will not be shared to comply with VISTA’s data security statement. All analyses will be performed in Python, version 3.9.12, primarily using the scikit-learn 1.7.1 and PyTorch libraries 2.7.0.

### 2.11. VISTA vs. the CHA_2_DS_2_-VASc Development Dataset

The CHA_2_DS_2_-VASc development dataset was extracted from the Euro Heart Survey (EHS) on AF, a multi-centre prospective observational study whose methods have previously been described [91]. Patients were enrolled in EHS if they were 18 years or older and had an electrocardiogram or Holter recording showing AF during the qualifying admission/consultation or in the preceding 12 months. The development study [92] screened EHS for patients with (1) absence of mitral stenosis and previous heart valve surgery, and (2) use of neither VKAs nor heparin at discharge. This yielded 1577 patients documenting all of the variables we have access to, with the addition of PAD. Outcome variables were thromboembolism (defined as AIS, peripheral embolism, or pulmonary embolism) and all-cause mortality at 1-year follow-up. Accounting for patients lost to follow-up, the development dataset comprised 1150 patients with known survival status and 1084 with known thromboembolic status at 1 year.

Our dataset and EHS enrolled patients from hospitals and acute centres across 38 and 35 countries, respectively. Our centres were globally distributed while the Euro Heart Survey was pan-European. Recruitment ran from 1992 to 2006 for the VISTA contributing trials and September 2003 to July 2004 for EHS. The differences in the eligibility criteria of VISTA’s contributing trials and EHS reflect their stroke- and AF-centric aims, respectively. Our less-stringent screening filters were a deliberate attempt to enhance the applicability of CHA_2_DS_2_-VASc to a broad subset of AF patients, not least because of the already stringent inclusion and exclusion criteria of VISTA’s contributing trials relative to that of the observational studies comprising EHS. Finally, the differences in outcome variables reflect our focus on secondary prevention as opposed to primary prevention.

### 2.12. Statistical Analysis

#### 2.12.1. Overview

We will validate the predictive performance of CHA_2_DS_2_-VASc for 90-day recurrence and secondary outcomes in the AF patient cohort by examining discrimination (AUC), calibration (calibration curves and Brier scores), and clinical utility (decision curve analysis). For CPR updating, we will use logistic regression (LR), extreme gradient boosting (XGBoost), and multilayer perceptron (MLP) models, with training and tuning performed through 5 × 2 nested cross-validation. The MLP model will employ transfer learning to incorporate information from the non-AF cohort. Model performance will be assessed on a hold-out test set using AUC, calibration curves, F1 score, and accuracy. We will utilise Shapley additive explanations (SHAP) for model interpretation and to construct two CPRs per model: one based on SHAP main effects and another incorporating both SHAP main and interaction effects. These CPRs will be evaluated against each other, CHA_2_DS_2_-VASc, and default strategies, with test tradeoff analysis to balance ease-of-use with clinical utility.

#### 2.12.2. Data Preprocessing

##### Missing Data Management Imputation

Routine missing data diagnostics will first be conducted: the proportion of missing values for each variable will be reported and visually illustrated by means of a missing data heatmap. The correlation of missingness between variables will be reported pairwise and a dendrogram will be used to provide a comprehensive visual representation of pairwise comparisons.

Multiple Imputation by Chained Equations using Random Forests (MICE RF) will be implemented to impute missing values, based on the algorithm proposed by Doove et al. [93]. Multiple imputation is today’s state-of-the-art solution for handling missing data and, by incorporating a recursive partitioning technique in the MICE framework, this method can fit interactions, non-linear relationships, and complex distributions within the data. As a result, more precise and reliable imputations are achievable as the gains in preserving interaction effects have been found to outweigh the somewhat higher biases for main effects [93], a tradeoff we consider justified given our presumption of interaction effects. Importantly, the missing data mechanisms assumed by MICE (missing completely at random [MCAR] or missing at random [MAR]) are almost impossible to definitively establish [94] and the missing data diagnostics mentioned above are suited only to intuit the plausibility of MCAR. To alleviate this issue, we will include available auxiliary variables in the imputation model that are predictive of missingness but will not be used in the data analysis stages, namely hyperlipidaemia, smoking status, and 30-day NIHSS. Incorporating auxiliary variables has been shown to make the MAR assumption more plausible [95,96], all the while posing little risk to the precision or bias of estimates.

To avoid information leakage, imputation will be performed strictly within each training fold of the inner and outer cross-validation loops, and never on the full dataset before splitting. Any necessary scaling or encoding of continuous variables (e.g., NIHSS, mRS, OTT, VKA days) will likewise occur within-fold. A total of 10 imputation cycles will be performed before aggregating the respective models’ outputs (i.e., computing the mean for continuous variables and selecting the mode for binary variables), with 100 trees per RF model. The constituent features of CHA_2_DS_2_-VASc will be imputed and the score calculated after imputation is complete, which has been reported to be the more appropriate approach for sumscores constructed from relatively few variables [94]. Of note, MICE RF will be performed separately for AF and non-AF cohorts because the validity of later analyses depends on the non-AF cohort having in no capacity shaped the models trained on the AF cohort.

Although missing data ubiquitously occur in RCTs, VISTA did not record how contributing trials handled missing data.

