### 2.4. Predictor Variables

The predictor variable in the validation analyses is CHA_2_DS_2_-VASc score, computed on the basis of its constituent features. It is computed as follows: 1 point for each of CHF, hypertension, DM, vascular disease (MI, CAD, or peripheral artery disease), age 65–74 years, and sex category (female), and 2 points for each of age ≥ 75 years and antecedents of AIS or TIA [24]. All features were measured at baseline, and, with the exception of age, all were binary encoded. As one of the more subjective items considered by CHA_2_DS_2_-VASc, peripheral artery disease was seldom recorded by contributing trials. Hence, MI and CAD will underlie the vascular disease feature.

The predictor variables in the updating analyses are the constituent features of CHA_2_DS_2_-VASc—omitting S_2_, which provides no discriminatory information in a cohort where all patients inherently have the same value (i.e., 2)—and previous stroke. Crucially, since secondary prevention is, by definition, aimed at patients having sustained an AIS, previous stroke is defined herein as any episode of AIS *prior* to the one that prompted recruitment. Besides preserving the familiar 7-feature structure of CHA_2_DS_2_-VASc, incorporating this variable in the updated CPR is very apropos in the modern-day context of effective treatment and demographic ageing which signify that many patients survive one or more strokes.

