### 2.6. Outcome Variables

The primary outcome variables are 90-day recurrence, defined as any episode of AIS within 90 days of the event that prompted recruitment. Of our 2763 AFAIS patients (and 7809 non-AF AIS patients), some will have no prior history of stroke while others will have suffered antecedents. Thus, our primary outcome variable includes second as well as third or *n*th strokes.

The secondary outcome variables are 7-day recurrence; 7- and 90-day HT; 90-day decline in functional status; and 90-day all-cause mortality. The 7-day recurrence is defined analogously to the primary outcome variable: any episode of AIS within 7 days of the event that prompted recruitment. The 7- and 90-day HT are defined as any episode of intracranial haemorrhage (ICH) within 7 and 90 days of the event that prompted recruitment, respectively.

Decline in functional status is defined as 90-day mRS score ≥ 2 for patients that were not disabled before stroke (pre-stroke mRS 0–1) and failure to return to pre-stroke mRS score at 90 days for patients that were disabled before stroke (pre-stroke mRS ≥ 2). In other words, progression on the scale qualifies as decline in functional status, with the exception of progression from mRS 0 to 1, seeing as even minor residual deficit post-stroke will, by definition, increase an mRS 0 patient to mRS 1.

To account for the fact that death within 90 days may preclude observation of 7- and 90-day recurrence, we will conduct a sensitivity analysis using a Cox proportional hazards model with mortality treated as a censoring event.

All contributing trials were double-blind RCTs, though no further details on blinded outcome assessment were accessible. Qualifications and demographic characteristics of outcome assessors were not available.

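### Imputing baseline score items from 30-day NIHSS, with draws collapsed to one value, can carry outcome information into the predictors and flatter the AUC by a small, missingness-dependent amount

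*Protocol article*

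**What the plan says.** Under Missing Data Management Imputation (section 2.12.2), missing values are filled by chained equations with random forests. To make the missing-at-random assumption more plausible, the article states that "we will include available auxiliary variables in the imputation model that are predictive of missingness but will not be used in the data analysis stages". Three such variables are then listed, the last of which is measured after baseline: "namely hyperlipidaemia, smoking status, and 30-day NIHSS". The constituent features of CHA2DS2-VASc "will be imputed and the score calculated after imputation is complete". Ten imputation cycles are combined by "computing the mean for continuous variables and selecting the mode for binary variables".

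The safeguard offered is fold separation: "To avoid information leakage, imputation will be performed strictly within each training fold of the inner and outer cross-validation loops".

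Section 2.4 says of the score items: "All features were measured at baseline". Section 2.6 defines the primary outcome as "any episode of AIS within 90 days of the event that prompted recruitment" and 7-day recurrence as "any episode of AIS within 7 days of the event that prompted recruitment". Haemorrhagic transformation has the same two windows. Section 2.12.4 validates CHA2DS2-VASc on the whole AF cohort, without a split. Under Imputation Diagnostics, a complete-case comparison is planned for the primary analyses.

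**The concern.** A rule scored at the index stroke can use only what is known then. Here, a missing baseline item may be filled from a severity measure taken on day 30. A recurrent stroke or haemorrhage before day 30 can raise that measure. If the item is associated with 30-day NIHSS among patients in whom both are observed, the imputation model will more often mark the item as present in patients who had the early event. The imputed predictor then carries a trace of the outcome it is meant to predict.

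Fold separation stops one patient's data from informing another patient's test prediction. It does not stop a patient's own day-30 status from filling in that same patient's baseline items, and the whole-cohort validation has no folds at all.

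At stake is optimism in the validation and test AUC. The Introduction reports C-statistics generally below 0.6 in patients with previous stroke. Table 1 labels 0.51–0.60 poor and 0.61–0.70 modest, so a shift of 0.01 to 0.02 near 0.60 could change the label.

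**Working it through.** **Timing.** Score items: baseline. 7-day outcomes: complete by day 7. Auxiliary NIHSS: day 30. Primary outcome: days 0 to 90. The auxiliary therefore follows every 7-day outcome and any 90-day event that occurs before day 30.

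**Size.** The plan states no figure to reproduce, so the size was explored by simulation.

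Input from the documents: N = 2763 (section 2.3). The assumed event rate of 10% lies within the article's 0.05–0.25 range.

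Assumed, not in the documents:
- 60% of recurrences fall before day 30, each adding 6 NIHSS points.
- Each risk item present adds 0, 1.5 or 3 points to 30-day NIHSS.
- CHF, hypertension, diabetes and vascular disease are each 5%, 20% or 40% missing completely at random.
- Logistic imputation models stand in for random forests. The baseline-only model uses age and sex.
- Ten draws, collapsed to the mode as planned or kept separate; 150 runs per setting.

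*Score with no true value, 30-day NIHSS in the model, outcome not in it, mode collapse.* Excess = AUC after imputation minus AUC with complete data:

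| Missing | 0 points per item | 1.5 points per item | 3 points per item |
|---|---|---|---|
| 5% | 0.5007 − 0.5005 = 0.0002 | 0.5017 − 0.5003 = 0.0014 | 0.4995 − 0.4966 = 0.0029 |
| 20% | 0.5014 − 0.5019 = −0.0005 | 0.5058 − 0.4995 = 0.0063 | 0.5113 − 0.4991 = 0.0122 |
| 40% | 0.5020 − 0.5029 = −0.0009 | 0.5149 − 0.5032 = 0.0117 | 0.5225 − 0.4993 = 0.0232 |

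Baseline-only imputation gave 0.497 to 0.503, in line with complete data. A second simulation of the same kind, also on assumed inputs and with mode collapse, gave 0.002–0.004, 0.009–0.016 and 0.019–0.030 at the three missing fractions when items were related to 30-day NIHSS. The excess was smaller when baseline NIHSS was also in the model and zero when items were unrelated. The upper ends quoted here come from that run.

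*What drives it.* At 40% missing and 3 points per item, keeping draws separate cuts the excess from 0.0232 to 0.5160 − 0.4993 = 0.0167, so pooling alone does not remove it. With 30-day NIHSS and the outcome both in the model and draws kept separate, AUC matched complete data within about 0.002 in every setting. With mode collapse it was still up to 0.5929 − 0.5825 = 0.0104 too high.

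*Truly predictive score (complete-data AUC about 0.58), 40% missing:*
- Plan's approach (30-day NIHSS, mode): 0.5696 − 0.5837 = −0.0141, 0.5828 − 0.5825 = 0.0003 and 0.5950 − 0.5845 = 0.0105 at 0, 1.5 and 3 points per item.
- Baseline-only, mode: losses of 0.0144, 0.0123 and 0.0134. At 5% missing the losses are 0.0013 to 0.0018.
- Baseline-only, draws kept separate: losses of 0.0173, 0.0159 and 0.0166. At 5% missing, 0.0020 to 0.0023.

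In this design the items were unrelated to age and sex, so the baseline-only model had almost nothing to work with. A model with informative baseline variables should lose less.

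**Scale.** Hanley–McNeil standard error at AUC 0.6 and 10% events: Q1 = 0.6/1.4 = 0.4286 and Q2 = 0.72/1.6 = 0.45. For 69 events among 691, √{[0.24 + 68 × 0.0686 + 621 × 0.09]/(69 × 622)} ≈ 0.038. For 276 among 2763 it is about 0.019.

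**The case against.** The strongest reply is that outcome-related variables belong in an imputation model. In proper multiple imputation they preserve the predictor–outcome association, and omitting them pulls the AUC towards 0.5. That stands as a general principle, and the simulation agrees. It does not cover this plan as written, because the draws are collapsed to one value. The article also does not say whether the outcome is in the model.

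Other points stand in part. Only imputed cells are affected, and section 2.3 describes the items as documented, so missingness may be low. The shift is within one standard error of the test-set AUC. It is, however, systematic and tends upwards. The updated rules and CHA2DS2-VASc share largely the same imputed items, so much of any inflation would be common to their comparison. The complete-case comparison could expose the problem, but it covers the primary analyses only.

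A reader might infer several stronger things that the documents do not support:
- That baseline NIHSS is left out of the imputation. Auxiliaries are defined as variables outside the analysis stages, so not being named there does not show exclusion.
- That early deaths add leakage. A day-30 value supplied from survivors' patterns carries no signal of that patient's death.
- That using any outcome-related variable in imputation is itself an error.
- That haemorrhage and 7-day outcomes are the worst affected. The timing makes them exposed, but only recurrence was simulated.

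**Conclusion.** The point holds as a conditional and usually small source of optimism. It does not invalidate the validation. The plan lets a day-30 measure fill baseline predictors, collapses the draws, and relies on a safeguard that does not address this route.

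For a score of no true value the excess in AUC is roughly 0 to 0.004 at 5% missing, up to about 0.016 at 20% and up to about 0.03 at 40%. For a truly predictive score the optimism is partly offset by attenuation, and the net error at 40% missing ran from about −0.014 to +0.011. All sizes rest on assumed missingness, assumed NIHSS effects and logistic stand-ins for random forests. They show a range and do not estimate the effect in this dataset. The true size depends on the unstated missing fraction and on how strongly the items relate to 30-day NIHSS.

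**What to change.** Amend Missing Data Management Imputation in three places:

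1. For hold-out test patients and for the whole-cohort validation, impute score items only from variables known at the index stroke, and name baseline NIHSS as part of that imputation model. Section 2.3 shows it is already extracted.
2. Report performance with and without 30-day NIHSS in the imputation model as a sensitivity analysis, for both the 7-day and the 90-day outcomes.
3. Compute performance in each imputed dataset and pool it, instead of collapsing the draws to a mode or mean first.

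The cost is a few lines of text and one further set of runs. There is also a statistical cost, and the plan should state it. Baseline-only imputation attenuates the AUC of a truly predictive score by about 0.002 at 5% missing and about 0.012 to 0.015 at 40% with mode collapse, or 0.016 to 0.017 in the simulation above when draws are kept separate. That attenuation also leans towards the article's own hypothesis that CHA2DS2-VASc discriminates poorly. It is nonetheless the conservative direction for a new rule and closer to what a user at stroke onset would obtain. Showing both results makes the trade-off visible.
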